**Data analysis**

*Interrupted time series*

A linear, segmented interrupted time series analysis will be used to evaluate the impact of the social media programme on HPV vaccination.

For the primary outcome, we will count the number of youths aged between 12 and before their 15
^th^ birthday who have received the HPV vaccination per month. Similarly, for the secondary outcome, we will count the number of young people aged up to 25 (inclusive) who have received the HVP vaccination per month. Our analysis models will include two segments: a pre-interruption period of 49 months, beginning on Jan 2020-Dec 2023, and a post-interruption period of 24 months, beginning on Jan 2024-Dec 2025, which encompasses both the intervention and post-intervention periods.

For each outcome, we will fit the following statistical model (Model 1), separately for the intervention and control series:

$$\text{Model}\;1:\log Y_{t}=\beta_{0}+\beta_{1}t+\beta_{2}I+\beta_{3}\left(t-T_{I}\right)I+\text{seasonal}+\text{offset}+\epsilon_{t}$$
where

$Y_{t}$
 is the outcome value at time t, and

$T_{I}$
 is the time of the interruption. The variable

I
 indicates the post-interruption segment, which is equal to 1 post the interruption and 0 before. Parameter

$\beta_{0}$
 is the intercept at the beginning of the series,

$\beta_{1}$
 is the slope in the first segment,

$\beta_{2}$
 is the level change between the expected value (based on the pre-interruption data) and the observed data, and

$\beta_{3}$
 is the difference in slope compared to

$\beta_{1}$
. The error term,

$\varepsilon_{t}$
 represents deviations from the fitted model, and we will assume these to have lag-1 autocorrelation. Seasonality will be accounted for by including two pairs of sine and cosine harmonics with periods of 12 and 6 months.
^
40,
41
^ Due to the changing of the vaccine schedule in the year following the interruption, the seasonal components will be phase shifted by six months for that year. The log of the relevant population (i.e. all Aboriginal youth aged between 12 and before their 15
^th^ birthday per month) will be included as an exposure offset to adjust for any changes to the population over time. We will assume a negative binomial distribution with a log link function. We will fit these models using the glarma package in R.
^
42
^

The effect measures of interest will be:
•Level change at the end of the social media campaign (i.e. three months post the beginning of the social media campaign).•Change in slope.

In addition to the above model, for both outcomes, we will also fit the following single model (Model 2) that incorporates both the intervention and control series:

$$\text{Model}\;2:\log Y_{t}=\beta_{0}+\beta_{1}t+\beta_{2}I+\beta_{3}\left(t-T_{I}\right)I+\beta_{4}G+\beta_{5}\mathrm{tG}+\beta_{6}\mathrm{IG}+\beta_{7}\left(t-T_{I}\right)\mathrm{IG}+\text{seasonal}+\text{offset}+\epsilon_{t}$$
where

$Y_{t},T_{I},I,t,\text{seasonal},\text{offset and}\;\epsilon_{t}\;$
are as described above.

G
 represents the series with a value of 1 representing the intervention series, and a value of 0 representing the control series.

$\beta_{0}$
,

$\beta_{1}$
,

$\beta_{2}$
 and

$\beta_{3}$
 are as described above for the control series.

$\beta_{4},\beta_{5},\beta_{6}\;\text{and}\;\beta_{7}$
 represent the interactions between time and the intervention series. Specifically,

$\beta_{4}$
 represents the difference in the intercept at the beginning of the series between the intervention and control series,

$\beta_{5}$
 represents the difference in slope between the intervention and control series in the first segment,

$\beta_{6}$
 represents the difference in the level change between the intervention and control series, and

$\beta_{7}$
 represents the difference in the change in slope between the intervention and the control series.

We will compare the estimates of level change at the end of the social media campaign and change in slope between Model 1 and Model 2. This comparison will allow us to assess the possibility of whether a co-intervention/concurrent event may explain our findings.
^
35
^

We will plot interrupted time series graphs for all outcomes and series using the recommendations of Turner et al.
^
43
^ These plots will include: data points, trend lines, seasonality estimation and confidence intervals surrounding the trend line and counterfactual estimates. Segments will clearly delineated by breaks in the trend lines.

Subgroup analysis

We will fit Model 1 for the primary and secondary outcomes for the intervention series separately by:
•Sex (Females, Males)•Location in Perth (North West, North East, Central, South West and South East)

Influencer data

All qualitative information will then be synthesised descriptively, key messages will be identified, with thematic analysis completed using Nvivo software.

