## Introduction

Human papillomavirus (HPV) is a common sexually transmitted infection that can lead to HPV-related cancers such as cervical cancer and other cancers such as anal, vaginal, and penile cancer.
^
1,
2
^ HPV rarely produces symptoms and cannot be cured or treated; therefore, vaccination is essential to protect against HPV and HPV-related diseases.

In 2007, Australia initiated the HPV vaccine through the National Immunisation Program (NIP) to girls aged 12 to 13 years in 2007 and to boys in 2013; catch up programs were implemented for older age groups. Up until 2023, the HPV vaccine provided as a free two-dose program for both males and females aged 12-13 years, with doses given between 5-6 months apart through school-based programs.
^
3
^ Responding to the global decline in HPV vaccination, lack of access to the vaccine and cost and burden required for two doses, WHO released updated recommendations in 2022 that a single dose was effective in reducing HPV.
^
4
^ As of 2023, Australia has transitioned to the single dose for 12-13 year olds through the NIP delivered at school with young people up to 26 years old also eligible for the free HPV vaccine. If a vaccine dose is missed at school, depending on their place of residence, a young person may receive a free catch-up dose at their school, their local Aboriginal or government health centre, or private general practitioner.

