**Outcomes**

The primary outcome, as defined by the World Health Organization and for reporting Australian reporting standards as a recipient of the HPV vaccination by the age of 15 years (ie before their 15
^th^ birthday).
^
37
^ Secondary outcome will be the number of young people who are the recipient of the HPV vaccination at 25 years old.
^
37
^

For Influencer analytics we will measure total number views, total likes, comments, and total shares. From our own social media platforms we’ll report on the average time each video was watched, whether a video was watched in full (percentage of viewers who watched the entire video), the source of where people found the videos and where the viewers were located.

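### The secondary outcome (vaccinations up to age 25) has no model term for the probable 2023 change in free access, so its slope change may be biased

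*Protocol article*

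**What the plan says.** In the protocol article, Data analysis: "for the secondary outcome, we will count the number of young people aged up to 25 (inclusive) who have received the HVP vaccination per month". (The Outcomes section words it differently: "Secondary outcome will be the number of young people who are the recipient of the HPV vaccination at 25 years old". The two need reconciling; this point uses the Data analysis definition.) The Data collection section requests register data for ages 12-25 for the whole of 2020-2025.

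On access, the Introduction says: "Up until 2023, the HPV vaccine provided as a free two-dose program for both males and females aged 12-13 years". It then says "As of 2023, Australia has transitioned to the single dose for 12-13 year olds through the NIP delivered at school", and the same sentence continues "with young people up to 26 years old also eligible for the free HPV vaccine". On older ages before that, it says only that "catch up programs were implemented for older age groups", without giving their ages or how long they ran.

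The offset is described as "The log of the relevant population (i.e. all Aboriginal youth aged between 12 and before their 15"th birthday, taken monthly, and it "will be included as an exposure offset to adjust for any changes to the population over time". That age band belongs to the primary outcome; the band for the secondary outcome is not spelled out.

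Models 1 and 2 have one linear trend up to December 2023, then a level change and a slope change. Neither has a 2023 term. The only allowance for a schedule change is a six-month shift of the seasonal terms in the year after the interruption. Model 2 adds the non-Aboriginal control series. The sex and location subgroups use Model 1 on the intervention series only.

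**The concern.** If ages above the school programme gained free access in 2023, the monthly count up to age 25 would be expected to rise for a reason unrelated to the campaign. The rise would fall in the last year of the pre-campaign segment, where a single straight line has to fit it. That line tilts upward and is projected over 2024-2025 as the counterfactual. The offset does not help, because it follows how many people live in Perth and not how many can have the vaccine free.

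Change in slope is one of only two effect measures named. A biased slope could make an ineffective campaign look as if uptake faded, hide a sustained gain in catch-up vaccination, or, with another pattern of uptake, credit the campaign with a gain it did not make. This holds even if a first dose is the counted event in every year, so it is separate from the move from two doses to one.

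**Working it through.** The article gives no figure for the secondary outcome to reproduce; its 85% power statement concerns the primary outcome and does not bear on this.

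**Inputs from the article**
- 72 monthly points, January 2020 (month 1) to December 2025 (month 72).
- Pre-interruption segment January 2020 to December 2023. The article calls this 49 months, but 4 × 12 = 48. The check uses 48/24, so the interruption is at month 49, and repeats with 49/23.
- January 2023 is month 37, so 49 - 37 = 12 pre-campaign months follow the change.
- Model 1: log E(Y) = β0 + β1·t + β2·I + β3·(t - T)·I + 12- and 6-month harmonics, negative binomial with log link.

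**Assumptions (not in the article)**
- No campaign effect, constant population, flat underlying rate.
- The count is multiplied by r from January 2023. The size and shape of r are unknown, so ranges are shown.
- The seasonal phase shift and the autocorrelation are left out of this fit.

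The model is fitted to noise-free expected counts, so any non-zero effect is bias.

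**Sustained step, Model 1**

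| r | β1 | β2 | β3 | slope change per month, exp(β3) - 1 | level ratio at 3 months, exp(β2 + 3β3) | ratio to counterfactual, Dec 2025, exp(β2 + 23β3) |
|---|---|---|---|---|---|---|
| 1.10 | 0.0023 | 0.010 | -0.0020 | -0.20% | 1.004 | 0.965 |
| 1.25 | 0.0055 | 0.021 | -0.0047 | -0.47% | 1.007 | 0.916 |
| 1.50 | 0.0102 | 0.033 | -0.0087 | -0.87% | 1.007 | 0.845 |

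For r = 1.50, the last column is exp(0.033 - 23 × 0.0087) = exp(-0.167), which is 0.845 before rounding of the inputs. With a 49/23 split, β3 is -0.0020, -0.0048 and -0.0088.

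**Other shapes, r = 1.50, Model 1** (build-ups linear on the log scale)

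| Shape from January 2023 | β3 | level ratio at 3 months |
|---|---|---|
| Sustained step | -0.0087 | 1.007 |
| Build-up over 12 months, then plateau | -0.0062 | 1.212 |
| Surge decaying with a 6-month half-life | -0.0076 | 0.849 |
| Build-up over 24 months | +0.0048 | 1.207 |
| Build-up over 36 months | +0.0092 | 1.117 |

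The slope bias can take either sign. The level change is nearly untouched only for the sustained step.

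**Model 2 (difference in slope change, β7), sustained steps**
- 1.50 in both series: -0.0001, in effect zero.
- 1.50 intervention, 1.25 control: -0.0045.
- 1.25 intervention, 1.50 control: +0.0044.

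**With a step term at month 37 in Model 1**
- Sustained step (r = 1.25 and 1.50): level change and slope change both return to zero.
- Refitting two of the other shapes at r = 1.50 with the same added term, the 12-month build-up still gives a level ratio of 1.20 at 3 months, and the decaying surge 0.84. The term fully corrects only a sustained step.

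**Cost in precision.** Generalised least squares on 72 months with first-order autocorrelation 0.3 and harmonics, step at month 37 or 38: the standard error of β1 rises by about 45-55% and that of β3 by about 4-5%.

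**The case against.** The Introduction does not plainly say that eligibility widened in 2023. The date governs the single-dose move, and access up to 26 follows in a subordinate clause that does not call it new. Earlier catch-up programmes are mentioned. If the older ages already had free access throughout 2020-2022, the problem shrinks or disappears. This stands: the change is probable on the article's wording, not established, and its size is an assumption.

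The controls were chosen in the same city so that shared events show up in both series, and with equal proportional responses Model 2 does cancel the bias. This also stands, but the article gives no figures suggesting that the groups responded equally at older ages, and the subgroup analyses have no control series.

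A reader might infer more than the article supports:
- **That the offset is fixed for 2020-2025.** It is monthly and meant to follow population change. Only its age band would stay the same, and for the secondary outcome that band is itself an inference.
- **That a false fall in slope is certain.** That follows for a sustained step. With uptake still building in 2024-2025 the sign reverses.
- **That the rate is understated by the share of ages without free access.** The plan does not estimate a rate per eligible person, and a constant share would go into the intercept. What matters is the change in the count in 2023.

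**Conclusion.** The point holds in a limited form. An access change probably falls inside the single linear pre-campaign segment of the secondary outcome, no term in either model represents it, and a population offset cannot absorb it. If it was a sustained rise of 10% to 50%, Model 1 shows a false slope change of about -0.2% to -0.9% per month, reaching 3.5% to 15.5% below the counterfactual by December 2025 (1 - 0.965 and 1 - 0.845). Other patterns of uptake can change the direction and bias the level. Model 2 is protected only under equal proportional responses.

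These sizes rest on assumed steps, a January 2023 start and a flat underlying rate. The point concerns the secondary outcome and its subgroups. The article does not show that the primary outcome is affected. It does not rule it out either: if 14-year-olds were among those newly eligible, they fall in the primary band (12 to before the 15th birthday), and the same check applies there.

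**What to change.** 1. State which ages had free access in 2020-2022 and the month in which that changed, and spell out the age band of the offset for the secondary outcome.
2. If access did widen in 2023, either (a) analyse the ages with free access throughout 2020-2025, with a matching offset, separately from the newly eligible ages; or (b) keep ages up to 25 together and add a 2023 step to Model 1, and the same step with a group interaction to Model 2, at least as a sensitivity analysis. Apply the same choice to the sex and location subgroups.
3. If 14-year-olds were newly eligible, run the same check for the primary outcome.

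Option (a) is the safer choice, because the series with constant access is free of this bias whatever shape the uptake took. The newly eligible series would have only about 12 pre-campaign months with access and should be read accordingly. Option (b) fully corrects only a sustained step.

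Cost: wording plus an age split or one or two model terms. No new data are needed, since the register request already includes date of birth and timing of vaccination. Option (b) raises the standard error of the pre-campaign slope by about 45-55%, but that of the slope change by only about 4-5%.

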**Controlled interrupted time series (CITS)**

This CITS study will be conducted over 72 months and includes three distinct periods: a 49-month pre-intervention period (2020-2023), a 4-month intervention period and a 19-month post-intervention period (2024-2025). ITS is a quasi-experimental design for assessing public health interventions and is a robust method when other designs such as randomised controlled trials are impractical. ITS study designs allow adjustment of potential biases such as secular trends, seasonal trends, random fluctuations, and autocorrelation compared to other quasi-experimental designs such as controlled before and after studies.
^
34
^ Inclusion of a control group can strengthen an ITS evaluation by allowing assessment of whether any observed impact of the intervention is likely causal, or could instead be due to co-interventions or other events occurring concurrently with the intervention.

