**Sample size**

Based on data from the Australian Bureau of Statistics, we anticipate approximately 89 Aboriginal youth turning 15 years old each month in Perth over the study period.
^
32
^ Using the primary outcome definition, monthly numbers of young people before their 15
^th^ birthday fully vaccinated against HPV, will be the unit of aggregation in the regression models. A total of 72 monthly data points (2020-2025) will provide 85% power to detect a one-standard-deviation shift in the average proportions post-intervention, at an α = 0.05 and a first-order autoregressive model with autocorrelation of 0.3.
^
38
^ Empirical research has shown autocorrelations of the order of 0.3 (median 0.33; IQR 0.03, 0.58; 36 ITS studies in public health).
^
39
^

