### Study status

Intervention started Feb 2024.

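### The segment counts and dates imply different interruption months: 49 + 24 = 73 in a 72-month series, and the printed dates put an unexposed January 2024 in the post segment

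*Protocol article*

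**What the plan says.** Four places in the protocol article bear on when the interruption falls.

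- **Controlled interrupted time series (CITS):** "This CITS study will be conducted over 72 months", divided into "a 49-month pre-intervention period (2020-2023), a 4-month intervention period and a 19-month post-intervention period (2024-2025").
- **Sample size:** "A total of 72 monthly data points (2020-2025) will provide 85% power". No split into segments is given there.
- **Data analysis:** two segments, namely "a pre-interruption period of 49 months, beginning on Jan 2020-Dec 2023, and a post-interruption period of 24 months, beginning on Jan 2024-Dec 2025". The second is said to cover the intervention and post-intervention periods together. The indicator I is 1 after the interruption and 0 before it. T_I is called the time of the interruption and is given no calendar month.
- **Study status:** "Intervention started Feb 2024".

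The effect measures are the level change at the end of the campaign, defined as three months after the campaign began, and the change in slope. Stage 2 says that the campaign starts before school term 1 but names no month.

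**The concern.** The sentence that defines the two segments cannot be carried out as written, because its count and its dates disagree. This is more than a slip of one. The segment boundary defines both I and (t − T_I)I in Model 1 and Model 2, so it enters the main estimates, the comparison between the two models and the subgroup fits. One reading puts the interruption at February 2024, when the campaign began. The other puts it at January 2024, so that a month with no campaign becomes the first point of the post segment. An untreated month in that position can pull the estimated level change towards zero and tilt the post-interruption slope upward. An interruption month left unsettled could also be chosen after the data are seen.

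**Working it through.** **1. Month counts**

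| Statement | Count printed | Count from its own dates or parts |
|---|---|---|
| Data analysis, pre segment, Jan 2020-Dec 2023 | 49 | 4 × 12 = 48 |
| Data analysis, post segment, Jan 2024-Dec 2025 | 24 | 2 × 12 = 24 |
| Data analysis, total | none printed | 49 + 24 = 73 |
| CITS section, three periods | 72 | 49 + 4 + 19 = 72 |
| CITS section, pre period labelled 2020-2023 | 49 | 48 |
| CITS section, intervention plus post-intervention | none printed | 4 + 19 = 23 |

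**2. What each reading implies.** Counted from January 2020, month 49 is January 2024 and month 50 is February 2024. A 49-month pre segment therefore puts the interruption at February 2024, with 72 − 49 = 23 months after it. That equals 4 + 19 and agrees with Study status. The printed dates give 48 + 24 = 72 with the interruption at January 2024. The post segment then has one month more than the intervention and post-intervention periods that it is said to contain.

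**3. The plan's own power figure.** Inputs from Sample size: 72 points, a shift of one standard deviation, α = 0.05 (two-sided assumed) and AR(1) autocorrelation 0.3. For a mean shift fitted by generalised least squares (GLS) with unit marginal SD, power = Φ(1/SE − 1.96).

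- 48/24 split: SE = 0.332; 1/0.332 − 1.96 = 1.05; power 85.4%.
- 49/23 split: SE = 0.335; 1/0.335 − 1.96 = 1.02; power 84.6%.

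The stated 85% is reproduced and does not depend materially on the disputed month.

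**4. Consequence if the printed dates are coded.** A true step of 1.00 on the log scale from February 2024 was projected by GLS onto the columns 1, t, I and (t − T_I)I. The fit was done without seasonal terms, and again with the 12- and 6-month harmonics and the six-month phase shift (applied to calendar 2024, an assumption). The named level measure is anchored to the campaign start, so it falls in May 2024. That is β2 + 4β3 when T_I is January and β2 + 3β3 when T_I is February.

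| Autocorrelation | T_I = Jan: β2 | T_I = Jan: β3 | T_I = Jan: May level change | T_I = Feb: May level change |
|---|---|---|---|---|
| 0 | 0.84 | 0.010 | 0.88 | 1.00 |
| 0.3 | 0.74-0.75 | 0.013 | 0.79-0.80 | 1.00 |

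Example at 0.3 without seasonal terms: 0.735 + 4 × 0.0133 = 0.788, an attenuation of 21%. With harmonics and phase shift: 0.747 + 4 × 0.0128 = 0.798, or 20%. At autocorrelation 0: 0.843 + 4 × 0.0100 = 0.883, or 12%. The true slope change is zero, so each β3 in the table is pure bias.

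**5. Sensitivity to the assumptions**

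- *Weight of January 2024.* The documents give no monthly counts, so its weight relative to other months was varied as an assumption. Over autocorrelation 0.3 to 0, the May level change is 0.79-0.88 at weight 1, 0.88-0.94 at 0.5, 0.94-0.97 at 0.25 and 0.98-0.99 at 0.1.
- *Late effect.* With an illustrative step that begins only in May 2024 (no seasonal terms), the May level change is 0.53-0.57 with T_I = January and 0.57-0.63 with T_I = February. The disputed month then accounts for only 0.04-0.06.

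**The case against.** The strongest reply is that this is a slip in a date label. T_I is never given a calendar month, the count of 49 appears twice, and the CITS split sums correctly only with a February interruption. An analyst who follows the count gets the right model and no bias. That stands, so the attenuation is conditional on the printed dates being coded. A reader might infer that the plan fixes the interruption at January and that its level change is therefore biased. The text does not support that, because the same sentence supports both months.

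Three other stronger readings also fail.

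- A reader might infer a loss of about a quarter from β2 alone (0.74 at autocorrelation 0.3). The immediate β2 is not one of the named effect measures; for the campaign-end level change the figure is 20-21%.
- A reader might infer that the time point for the level change moves by a month. It is tied to the start of the campaign, so with a February start it is May under either coding.
- A reader might infer that the power statement needs revision. It names no split, and 85% holds for both.

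The size is also open to challenge. The planned model is negative binomial, in which low-count months carry less information. Much vaccination is delivered at school, and the campaign was to begin before term 1, so January may well be a low month. The campaign plan has brand launch in weeks 1-6, peak posting in weeks 8-12 and access to vaccination after week 12, which argues against a full step in February. Both points stand, and both reduce the bias due to this one month. Neither removes the contradiction.

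**Conclusion.** The point holds as a contradiction that must be reconciled, with a conditional consequence. It is certain that the pre segment is printed as 49 months with dates that span 48, that the segments add to 73 against a stated 72, and that the dates place the boundary one month before the stated start of the campaign. February 2024 is the only interruption month that agrees with the CITS counts, the 72-month total and Study status together.

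If the printed dates are coded, the campaign-end level change is attenuated by about 12% at autocorrelation 0 and 20-21% at the protocol's own 0.3. The slope change is biased upward by about 0.010-0.013 per month per unit step. These sizes rest on a Gaussian AR(1) stand-in for the negative binomial model, an immediate step in February and equal monthly weights. They could shrink to a few per cent under the alternatives shown, and they are zero if the 49-month count is coded. The text is wrong as written. The case for correcting it rests on the contradiction in the quantity that defines the analysis, not on any one percentage.

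**What to change.** In Data analysis, replace the segment sentence with: pre-interruption January 2020 to January 2024 (49 months); post-interruption February 2024 to December 2025 (23 months, made up of the 4 intervention and 19 post-intervention months); T_I = February 2024; total 72 months. In the CITS section, relabel the 49-month period as January 2020 to January 2024 and start the later periods at February 2024. Leave the power statement as it is.

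The cost is one sentence and one set of labels. No data, model or sample size changes. The correction should be made and dated before the outcome series is analysed.

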### Immunisation program impacts

In Australia, the prevalence of the HPV types in women aged 18 to 24 years old which were targeted by the vaccine declined significantly from 28.7% in the pre-vaccination era (2005-2007), to 2.3% in vaccinated women after vaccine introduction (2010-2012).
^
5
^ The rate of high-grade cervical disease has also declined dramatically, by 2014 it dropped to less than half the 2007 rate in women under 20 years of age.
^
5
^ The introduction of the Gardasil 9 vaccine is expected to prevent up to 90% of cervical cancers. Some research suggests that increased HPV vaccination, together with greater participation in screening, has the potential to eliminate cervical cancer in Australia and elsewhere within a few decades.
^
5,
6
^

In Australia, young Aboriginal and Torres Strait Islander (hereafter, respectfully, Aboriginal) people do not receive their HPV vaccine dose, resulting in missed opportunities to be protected from HPV-related cancers.
^
4
^ This is particularly important as rates of cervical cancer in Aboriginal women are twice those of non-Indigenous women, mortality rates more than three times higher, and screening participation rates lower.
^
6–
9
^ The recent change to one HPV dose will have substantive impact on meeting the recommended dose proposed by WHO.
^
4
^ In 2022, the Australian national rate of having at least one dose of HPV vaccination for young people turning 15 years old was 83.0% for Aboriginal females and 78.1% for Aboriginal males.
^
10
^ In Western Australia (WA), the completion rates were 81.4% of Aboriginal females and 78.6% of Aboriginal males. Despite these overall rates being reasonable, there are pockets of concern within Western Australian, including the capital of the State, Perth. In 2022, 51% of Aboriginal young people in Perth received one dose of HPV vaccine during Year 7 and this did not improve in 2023 (unpublished data).
^
11
^ Substantive resources are needed to improve these rates both in school catch-up programs and within the community. To eliminate cervical cancer, improving HPV vaccine rates amongst young Aboriginal people is necessary.

Despite the decline in HPV, there are a number of reported barriers associated with HPV vaccine uptake including adolescents’ lack of awareness and knowledge, not feeling informed, and parental concerns around sexual activity and vaccine safety.
^
12

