## Protocol

### Setting and target population

This public health project will be delivered to male and female young Aboriginal people in the capital city of Western Australia (Australia), Perth. We have concentrated this project in Perth as i) it is not feasible to co-create effective health promotion messages for all regions of Western Australia due to geographic size (2.646 million km
^2^), and ii) given the large population of young Aboriginal people in the metropolitan area, we are able to effectively evaluate the impact of this project. Our primary target population will be young Aboriginal people aged 12-16 years old. The minimum age of involvement in the study is defined by the age that young people receive the vaccine at school and our maximum age is based on one-year post the age that is used for international reporting of HPV vaccination completion (see primary outcome). In 2023, we estimated 4983 young Aboriginal people aged 12-16 years old living in Perth.
^
32
^

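### One straight line covers both the 2024 campaign and all of 2025, so an effect that does not carry fully into 2025 yields a negative slope change even if the campaign worked

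*Protocol article*

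**What the plan says.** All references are to the Protocol article. Under Controlled interrupted time series (CITS): "This CITS study will be conducted over 72 months and includes three distinct periods", of 49, 4 and 19 months (pre-intervention, intervention, post-intervention).

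Data analysis keeps the pre-period as its own segment and merges the other two into a 24-month segment from January 2024 to December 2025, "which encompasses both the intervention and post-intervention periods". The form is fixed as well: "A linear, segmented interrupted time series analysis will be used to evaluate the impact of the social media programme on HPV vaccination". Model 1 therefore has one level term (β2) and one slope term (β3) for everything after the interruption, and Model 2 has the same terms plus their contrasts with the control series (β6, β7). Two effect measures follow, with no ranking: the level change three months after the campaign begins, and the change in slope.

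The campaign is placed in one year, from before term 1 to term 3. Study status gives February 2024 as the start. Under Setting and target population: "Our primary target population will be young Aboriginal people aged 12-16 years old". The primary outcome is a monthly count of vaccinated youths aged 12 to under 15, with the population of that age as offset. The Introduction places the routine school dose at age 12-13.

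**The concern.** The population at risk turns over. Each month some youths turn 12 and enter, and others turn 15 and leave. Routine vaccination happens mainly once, at school. A youth vaccinated at 12-13 in 2025 was about 11-12 in 2024, so many 2025 recipients were probably not yet in the target age band while the campaign ran. Their doses enter the same post-interruption segment as those of youths who were targeted.

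If the effect is smaller in 2025 than in 2024, for this reason or because it fades, a single straight line can only represent the step down as a decline from launch onward. The plan would then report a negative change in slope as a result for the campaign. One slope cannot tell cohort turnover from fading, and neither means that the campaign failed in the youths it reached.

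Model 2 does not help. The control series has no campaign effect to lose, so the decline passes into β7. The planned comparison of Models 1 and 2 would then mark it as specific to the intervention series.

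**Working it through.** **Period lengths.** 49 + 4 + 19 = 72 months, as the design section states. The analysis section's 49 + 24 is 73, and January 2020 to December 2023 is 48 months. With a February 2024 start, 49 months precede the campaign. I therefore ran both codings: post segment from February 2024 (49 + 23) and from January 2024 (48 + 24). The ranges below partly reflect this ambiguity.

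**Who is counted in 2025.** The band from 12 to under 15 holds 36 monthly birth cohorts. At the end of December 2025, those who had not turned 12 by the end of September 2024 number 15 (15/36 = 42%). Those who had not turned 12 by the end of May 2024 number 19 (19/36 = 53%). Earlier months of 2025 have smaller shares. For doses, Immunisation program impacts states: "In 2022, 51% of Aboriginal young people in Perth received one dose of HPV vaccine during Year 7". Uptake by age 15 in Western Australia is 81.4% (females) and 78.6% (males), about 80%. Then 0.51/0.80 = 64% of doses before 15 fall in Year 7 (range 63-65%), leaving 36%. This mixes Perth and state figures and is an assumption.

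**Noise-free fits.** I set the log effect to log 1.20 = 0.1823 from February 2024, with 2025 set by scenario, and fitted Model 1's mean structure by least squares, with and without the 12- and 6-month harmonics (the planned phase shift was not modelled). The 1.20 is an assumption. When 36% persists, the 2025 ratio is 1 + 0.36 × 0.20 = 1.072.

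- Slope ratio per year = exp(12·β3)
- Level at three months = exp(β2 + 3·β3)
- Fitted ratio at December 2025 = exp(β2 + k·β3), with k = 22 (February coding) or 23 (January coding)

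Example (nothing persists in 2025, February coding, no harmonics): β2 = 0.2180, β3 = -0.01189. Slope ratio exp(-0.143) = 0.87; level exp(0.2180 - 0.0357) = 1.20; December 2025 exp(0.2180 - 0.2616) = 0.96.

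| True 1.20 effect | Slope ratio per year (Feb; Jan coding) | Level at 3 months (Feb; Jan) | December 2025 (Feb; Jan) |
|---|---|---|---|
| Persists fully | 1.00; 1.02 | 1.20; 1.17 | 1.20; 1.22 |
| Through 2024, 36% in 2025 | 0.91-0.92; 0.93-0.94 | 1.20-1.21; 1.18-1.19 | 1.04; 1.06 |
| Through 2024, none in 2025 | 0.86-0.87; 0.88-0.89 | 1.20-1.21; 1.18-1.19 | 0.96; 0.97 |
| Four intervention months only | 0.92; 0.93-0.94 | 1.08-1.09; 1.08 | 0.96; 0.97 |

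Weighting the fit for AR(1) 0.3 changes little under the February coding. Under the January coding it lowers the level to 1.15 and gives slopes of about -5% and -10% per year in rows 2 and 3. A fully persistent effect also drops to 1.15 there, so that loss comes from the start month and not from the merged segment.

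**With noise.** A negative binomial simulation with both harmonics (300 runs per scenario; dispersion 0.05, seasonal shape and independent errors assumed) agrees. Share of runs with a significantly negative slope:

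- True ratio 1.20: 31% if the effect is in 2024 only, 13% if 36% persists, 3% if it persists fully.
- True ratio 1.40: 80%, 39% and 4%.

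At 1.20 the three-month level was 1.22, 1.19 and 1.20 in these scenarios.

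**Cost of a separate 2025 segment.** From SE² = c′(X′V⁻¹X)⁻¹c with AR(1) 0.3, adding a 2025 level and slope multiplies the standard error of the three-month level change by 1.03 to 1.04. With independent errors the factor is 1.05 to 1.07.

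**The case against.** The plan states the merge openly, and its first-listed effect measure largely does its job. If the effect lasts through 2024, the three-month level change recovers it whether or not anything survives into 2025. This stands. A reader might infer that a working campaign would look like no campaign at all; the figures do not support that, because no effect gives a level ratio of 1.00, not about 1.20.

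A reader might also infer that the late estimate falls below null. That needs no 2025 effect at all, even among youths who were exposed. With 36% persisting, the December 2025 ratio is 1.04 to 1.06. The attenuated level of 1.08 to 1.09 comes from an effect that stops after four months, which is rapid fading and not cohort turnover.

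Being under 12 is not the same as being unexposed. Families are targeted separately, and the protocol expects peer-to-peer posts and a lasting brand, so some carry-over to the next intake is plausible. The documents do not give the 2025 intake's age in 2024. At population level, a slope that falls because the benefit misses the next intake is a legitimate description of waning, and the planned plots would show a step.

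These points narrow the concern but do not remove it. Change in slope remains an unranked effect measure, and one line cannot show whether a negative value reflects turnover, fading or poor fit.

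**Conclusion.** The point holds in a limited form. Two of the three design periods, not all three, share one level and one slope. For a true ratio of 1.20 lasting through 2024, the change in slope is about -6% to -9% per year if 36% of the effect persists in 2025 and about -11% to -14% if none does. The three-month level change stays at about 1.18 to 1.22 in both cases. It drops to about 1.08 to 1.09 only if the effect is confined to the four intervention months. With full persistence there is essentially no negative slope.

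This rests on assumptions: the size of 1.20, the 64%/36% split, the inferred age of the 2025 intake, and incomplete carry-over into 2025, which the documents neither state nor exclude. They do not support the stronger reading that the plan would miss a real effect or turn it into harm. What is at risk is the reading of the slope and of the late-period estimates.

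**What to change.** - In Models 1 and 2, end the first post-interruption segment at December 2024 and add a separate 2025 segment with its own level and slope, at minimum as a prespecified sensitivity analysis.
- Report the 2024 contrast as the campaign effect and the 2025 contrast as persistence or spill-over. Do not interpret a single 2024-2025 slope change as a campaign effect.
- Use date of birth, which is already among the requested register fields, to show 2025 doses separately for youths who were 12 or older during the campaign and those who were not.
- Fix the interruption month (January or February 2024) and the end of the campaign (given as three months, four months or term 3), since the segments depend on both.

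The cost is a few model terms and some wording, with no new data. The interval for the three-month level change widens by about 3% under AR(1) 0.3, and the 2025 contrast, resting on 12 months, is less precise.
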